### Delivery of the interventions

The interventions will be delivered over a period of 7 to 10 weeks to participants in the communities where they live or work. At least 20 research assistants will help in the field recruitment, administration of the intervention, follow-up of participants in the community, and administration of the outcome assessment tool. Each research assistant will be allocated about 25 participants to follow up through the duration of the study. The research assistants will visit all their allocated participants every week, delivering the interventions on portable media players to an average of four participants per day. In this study setting this approach is currently the most practical and most reliable way of delivering the interventions for this trial.

One-time brief interventions have not been shown to improve knowledge of evidence-based medicine principles [35, 36] among health workers. So, as part of our intervention, at every visit we will play a recap of the previous episodes before playing the new episodes. Each participant will receive at least one supervised listening session of every episode, delivered by the research assistants over 7 to 10 weeks. In addition to the messages delivered by the research assistants, we will provide participants with the complete podcast on MP3 players, so that they can replay the episodes at their convenience. For the intervention group we will start with simpler concepts and gradually introduce more difficult concepts as the podcast series progresses, as summarised in Table 5 below. For the control group we will introduce episodes with health conditions that are similar to those being delivered in the intervention group at a defined period of time. The timing of study procedures is summarised in Fig. 2 below.

**Table 5 Tab5:** Sequence of delivery of the episodes of the podcast

Week/Visit	1	2	3	4	5	6	7
Episode	Intro	1 + 2	3 + 4	5 + 6	7 + 8	9	Evaluation^a^

^a^Study evaluation tool (Additional file 3).

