After removing some questions, we modified the remaining questions that did not perform well according to the Rasch analysis, and revised and simplified the text where needed. The items were also translated into Luganda and adapted for audio administration. In the second psychometric testing, the Claim Evaluation Tools were administrated to a similar sample as described in the first psychometric test, but approximately half of the sample received the items as a written questionnaire in English and the other half received the Luganda audio versions. The results of this test suggested that the items administered in English performed very well according to the Rasch model, and with high reliability. Furthermore, the items were also less difficult than what was found in the first psychometric testing before the revisions. The results also suggested that the Luganda versions of items had evidence of under-discrimination and differential item functioning in seven out of 29 items. These items were revised to improve fit to the Rasch model.

Based on these two psychometric tests, a selection of 18 multiple-choice items addressing the nine concepts that the IHC podcast covers will be used (Additional file 3). Each key concept is evaluated by two items. We chose items with high reliability (fit to the Rasch model) and those with an appropriate difficulty level.

Parents in both arms of the trial will complete the questionnaires after they have listened to the podcast or public service announcements. Research assistants will deliver the questionnaires, ensuring that the parents have adequate time to answer the questions and ensure that the questionnaires have been completed fully.

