### Blinding

Because of the nature of the intervention, the research assistants who will deliver the intervention, the principle investigator supervising them, and the participants in the study will not be blinded. The statistician who will analyse the study results will not be told which group is the intervention group until after the analyses are completed.

To ensure uniform performance in delivery of the intervention and assessment of outcomes, all study staff will receive joint training before the start of the trial and will receive refresher training in the course of the trial. We will have standard operating procedures to guide interactions with participants.

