### Analysis

We will present participants’ age, sex, and highest level of education attained as frequencies and proportions.

For the primary and secondary outcomes, we will use fixed-effect models with the stratification variable (education) modelled as a fixed effect, using logistic regression for dichotomous outcomes, linear regression for continuous outcomes and Poisson regression for count outcomes. For the questions that assess applied knowledge or understanding, missing values will be counted as ‘wrong’ answers.

We will report the proportion (for dichotomous outcomes), mean and standard deviation (for continuous outcomes), or median and interquartile range (for count outcomes) in each group, the estimated difference, the estimated confidence interval for the difference, and the *P* value for the difference between groups from the statistical model for each of the primary and secondary outcomes. For attitudes and intended behaviours (Additional file 3), we will dichotomise each outcome by combining, for example, ‘very unlikely’ with ‘unlikely’ and as ‘likely’ with ‘very likely’; and we will report the proportion in each of the four categories.

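### About 20 research assistants each deliver to and test a caseload of about 25 parents; adjusting for assistant would be a cheap gain in precision, with a check on whether the effect varies between them

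*Protocol article*

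**What the plan says.** Under Delivery of the interventions, the protocol article states that "At least 20 research assistants will help in the field recruitment, administration of the intervention", follow-up and "administration of the outcome assessment tool". It then says "Each research assistant will be allocated about 25 participants to follow up through the duration of the study". They visit weekly and play the recordings on portable media players.

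Under Outcome assessment, "Research assistants will deliver the questionnaires, ensuring that the parents have adequate time to answer the questions". Under Data collection and management, parents who listen in Luganda but cannot read it get a standardised audio version of the test, and an assistant writes down their answers.

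Under Blinding, "the research assistants who will deliver the intervention, the principle investigator supervising them, and the participants in the study will not be blinded". The same section treats uneven performance as something to control: "To ensure uniform performance in delivery of the intervention and assessment of outcomes, all study staff will receive joint training". Refresher training and standard operating procedures are added.

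Table 7 is one sheet per research assistant. It has a Group column, a column for each session and a column for the Claim Evaluation Tool.

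Under Analysis, for the primary and secondary outcomes, "we will use fixed-effect models with the stratification variable (education) modelled as a fixed effect". The regressions are logistic, linear or Poisson. No assistant term, random effect or clustered variance is named.

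**The concern.** Parents who share an assistant share a deliverer and, as Table 7 implies, a tester. Their scores may be more alike than those of parents with different assistants. The article recognises this risk and meets it with training, but the model it states leaves the assistant out.

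Two separate things could follow:

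- **Differences in level.** Some caseloads score higher than others in both arms. Left out of the model, this variation goes into the residual and wastes precision.
- **Differences in effect.** The gap between arms is larger under some assistants than others. The ordinary standard error misses this component, so intervals are too narrow for an effect meant to hold with other assistants.

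The text also does not say whether a parent's assistant is set before or after allocation, and no rule keeps both arms in each caseload. Randomisation is stratified by education and school arm, not by assistant.

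**Working it through.** **Inputs from the article.** At least 20 assistants with about 25 parents each; 397 parents needed for analysis; 20% loss to follow-up; 1:1 allocation; pass rates of 10% and 20%.

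**Consistency of the plan's figures.** 20 × 25 = 500, in line with the stated 497, and 397/0.80 = 496.25, rounded up to 497. The 397 is used here only as the number analysed; whether it matches the stated power is a separate question.

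**Assumed inputs.** The article gives no ICC (ρ) and no SD of the effect between assistants (τ, in score SDs). I take ρ = 0.02, 0.05, 0.10 and τ = 0.1, 0.2. The score formulas use a total SD of 1 and both arms in every caseload.

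**1. Differences in level only**

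Adjustment reduces the variance from 4/N to 4(1 − ρ)/N, so the equivalent number analysed is 397/(1 − ρ). In exactly balanced caseloads the unadjusted standard error is too large by 1/√(1 − ρ), so the unadjusted type I error is 2[1 − Φ(1.96/√(1 − ρ))].

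| ρ | Equivalent analysed | Unadjusted type I error, balanced caseloads |
|---|---|---|
| 0.02 | 397/0.98 = 405 | 4.8% |
| 0.05 | 397/0.95 = 418 | 4.4% |
| 0.10 | 397/0.90 = 441 | 3.9% |

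Simulation of 20 assistants × 20 parents in balanced caseloads gave 4.4% at ρ = 0.05 and 3.6% to 3.8% at ρ = 0.10. A separate simulation with assistants crossed with arm gave 5.0% and 5.05%. None of these shows inflation.

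**2. Differences in effect, no differences in level**

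True variance = 4/397 + τ²/20, against 4/397 = 0.01008 in the model.

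- τ = 0.1: 0.01008 + 0.00050; SE ratio √1.050 = 1.02; type I error 2[1 − Φ(1.96/1.0245)] = 5.6%.
- τ = 0.2: 0.01008 + 0.00200; SE ratio √1.199 = 1.09; type I error 2[1 − Φ(1.96/1.0948)] = 7.3%.

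For the pass rate, the variance at 10% and 20% is (0.09 + 0.16)/198.5, giving SE 0.0355. An effect SD of 2 or 5 percentage points makes it 0.0358 or 0.0372, with type I error of 5.2% or 6.2%.

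**3. Both together, balanced caseloads, ρ = 0.05, τ = 0.2**

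True variance = 4 × 0.95/397 + 0.04/20 = 0.00957 + 0.00200 = 0.01157.

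- Without an assistant intercept: SE ratio √(0.01157/0.01008) = 1.07; type I error 6.7% (simulations: 6.1% and 6.6%).
- With an assistant intercept: SE ratio √(0.01157/0.00957) = 1.10; type I error 7.5% (simulations: 6.7% and 7.3%).

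So the intercept recovers precision but does not deal with variation in effect. It also removes the slack that partly offset that variation. An assistant-level analysis held about 5% in every balanced setting simulated.

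**The case against.** The strongest reply is that the trial is individually randomised and the treatment is a recording. Assistants do not teach the content, parents can replay it on their own MP3 players, and the test is multiple choice or standardised audio. Variation in effect should therefore be small. On a normal score, moving from 10% to 20% passing is 1.28 − 0.84 = 0.44 SD, so an effect SD of 0.2 is already nearly half of the target effect; larger values are unlikely. If the podcast has no effect under any assistant, randomisation keeps the error at 5%. All of this stands, and it is why the point is small.

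It may also be said that such detail belongs in an analysis plan that is not shown. That stands only in part, because the article does state its model and the model names education alone.

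A reader might infer two stronger things. One is that any likeness within caseloads makes the error rate too high; step 1 of the working shows otherwise when both arms share each caseload. The other is that caseloads could be single-arm, so that assistant and arm are confounded. The documents do not support this. Parents are allocated individually by sealed envelope, and the per-assistant sheet in Table 7 has a Group column. The article never says outright that every caseload is mixed, which is a reason to state it, not evidence that it is not.

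**Conclusion.** The point holds as a cheap improvement, not as a threat to the validity of the trial. Leaving out the assistant gives up the equivalent of about 8 to 44 parents on 397 (405 − 397 to 441 − 397), or roughly 2% to 11%, at an assumed ICC of 0.02 to 0.10. It does not inflate the type I error through differences in level.

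If assistants also differ in effect, intervals are too narrow for inference beyond these assistants. The type I error is then about 5.6% to 7.3% at an assumed effect SD of 0.1 to 0.2 score SDs without level differences, and lower in balanced caseloads when assistants also differ in level. For the average effect over these assistants alone, the intervals are not too narrow.

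The conclusion rests on caseloads that hold both arms and on each assistant testing their own parents. Both are inferred from Table 7. The ICC and the effect SD are assumptions, since the documents give neither.

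**What to change.** 1. **Conduct.** Name the research assistant for each parent before the allocation call, and state that every caseload is to hold both arms in near-equal numbers.
2. **Primary models.** Add research assistant as a random intercept, next to education, in the models for both primary outcomes. This is for precision.
3. **Sensitivity analysis.** For both primary outcomes, either add an assistant-by-arm random effect or use standard errors clustered on assistant with a small-sample correction, as there are only about 20 assistants. This step addresses variation in effect, which the intercept does not.

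The cost is a few lines of analysis text and one identifier that the Table 7 checklist already records. The downside is one or two extra variance parameters and a mild constraint on assigning caseloads.

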**Fig. 2 Fig2:**
[figure not shown]
Schedule of enrolment, interventions, and assessments

### Outcome assessment

We will use a modified version of the Claim Evaluation Tools as the outcome measure [37]. The Claim Evaluation Tools consist of multiple-choice questions that assess an individual’s ability to apply 32 concepts that people need to be able to understand and apply to assess the validity of treatment claims and to make informed health care choices. In addition, it includes questions that assess intended behaviours, self-efficacy, attitudes, and satisfaction. Development of the Claim Evaluation Tools has been based on extensive qualitative and quantitative feedback from methodological experts, health professionals, teachers, and members of the public. We have conducted psychometric testing and Rasch analysis with a diverse sample of 1000 people, including P.5 children exposed to pilot versions of the IHC primary school resources, children who were not exposed, adults with little or no exposure to the concepts, and adults who are familiar with the concepts. The evaluation tool was found to have high reliability (Cronbach’s alpha 0.81), and to be unidimensional (there was no evidence of subdimensions measuring different traits). Furthermore, there was weak or no dependence between items (no items were redundant). Results from the pilot revealed that parents in the intervention group performed slightly better compared with those in the control group. Many of the participants in the pilot preferred Luganda to English and had difficulty reading the questions in English.

After removing some questions, we modified the remaining questions that did not perform well according to the Rasch analysis, and revised and simplified the text where needed. The items were also translated into Luganda and adapted for audio administration. In the second psychometric testing, the Claim Evaluation Tools were administrated to a similar sample as described in the first psychometric test, but approximately half of the sample received the items as a written questionnaire in English and the other half received the Luganda audio versions. The results of this test suggested that the items administered in English performed very well according to the Rasch model, and with high reliability. Furthermore, the items were also less difficult than what was found in the first psychometric testing before the revisions. The results also suggested that the Luganda versions of items had evidence of under-discrimination and differential item functioning in seven out of 29 items. These items were revised to improve fit to the Rasch model.

Based on these two psychometric tests, a selection of 18 multiple-choice items addressing the nine concepts that the IHC podcast covers will be used (Additional file 3). Each key concept is evaluated by two items. We chose items with high reliability (fit to the Rasch model) and those with an appropriate difficulty level.

Parents in both arms of the trial will complete the questionnaires after they have listened to the podcast or public service announcements. Research assistants will deliver the questionnaires, ensuring that the parents have adequate time to answer the questions and ensure that the questionnaires have been completed fully.

### Absolute standard (for passing scores)

We will use an absolute (criterion referenced) standard to set a passing score for the version of the Claim Evaluation Tools that we will use, i.e. based on how much the parents know and are able to apply. Parents will be counted as ‘passing’ or ‘failing’ depending on whether they meet a specified criterion. We used a combination of Nedelsky’s [38] and Angoff’s [39] methods to determine the criterion, which is a cut-off for a passing score, as described in Additional file 4. In addition, we determined a second cut-off for a score that indicates mastery of the nine concepts, using the same methods, as described in Additional file 4. The criterion for passing is a minimum of 11 out of 18 questions answered correctly. The criterion for mastery is a minimum of 15 out of 18 questions answered correctly.

### Primary outcomes

The difference between the intervention and control groups in the proportion of participants with a passing scoreThe mean difference in the score (number of correct answers) for all of the questions that assess their ability to apply the nine concepts that are included in the IHC podcast

### Secondary outcomes

The difference between the intervention and control groups in the proportion of parents with a score indicating mastery of the concepts (see above)The difference between the intervention and control groups for each conceptDifferences in attitudes and intended behaviours between the two groups

The intervention and control groups will complete the Claim Evaluation Tools after listening to all of the IHC episodes or public service announcements, respectively. We will evaluate the effects of the IHC podcast series again after 1 year, using the same outcome measures. We will try to locate participants who will have moved from their original residence or work place and document those who are lost to follow-up, as well as the reasons, where possible.

### Blinding

Because of the nature of the intervention, the research assistants who will deliver the intervention, the principle investigator supervising them, and the participants in the study will not be blinded. The statistician who will analyse the study results will not be told which group is the intervention group until after the analyses are completed.

To ensure uniform performance in delivery of the intervention and assessment of outcomes, all study staff will receive joint training before the start of the trial and will receive refresher training in the course of the trial. We will have standard operating procedures to guide interactions with participants.

### Data collection and management

#### Postrecruitment retention strategies

We will maintain a database of participants’ contact details and maps to their homes to enable follow-up. The research assistants will keep a study logbook and use a progress tracking checklist (Tables 6 and 7) to keep track of their progress and note any problems with follow-up of participants. We will discuss these problems and ways of addressing them and preventing loss to follow-up at weekly meetings.

**Table 6 Tab6:** Study log for monitoring progress of the intervention for each study participant

Study number _____________			Date enrolled ____________	Study arm _____
Visit number	Date contacted by phone	Date seen	Date intervention was administered	Observations and comments for study visit
ᅟ	ᅟ	ᅟ	ᅟ	ᅟ
ᅟ	ᅟ	ᅟ	ᅟ	ᅟ
ᅟ	ᅟ	ᅟ	ᅟ	ᅟ

**Table 7 Tab7:** Sample study procedures checklist for all participants

Research assistant: ________________ Contacts________ Date started_________											
	Participant particulars			Dates for study procedures and visits							
ID	Name	Group	Contacts	Consent	Intro	1–2	3–4	5–6	7–8	9	Claim Evaluation Tool
ᅟ	ᅟ	ᅟ	ᅟ	ᅟ	ᅟ	ᅟ	ᅟ	ᅟ	ᅟ	ᅟ	ᅟ
ᅟ	ᅟ	ᅟ	ᅟ	ᅟ	ᅟ	ᅟ	ᅟ	ᅟ	ᅟ	ᅟ	ᅟ
ᅟ	ᅟ	ᅟ	ᅟ	ᅟ	ᅟ	ᅟ	ᅟ	ᅟ	ᅟ	ᅟ	ᅟ

### Data collection and management

We will use paper questionnaires for the outcome assessment and we will collect baseline sociodemographic characteristics using a paper form. For participants who prefer listening to the Luganda version of the podcast but are unable to read Luganda we will use an interviewer-administered, standardised Luganda audio version of the evaluation tool. A research assistant will enter their responses to the audio evaluation tool on a paper questionnaire. To reduce any wrong entries and missing values the research assistants will check the questionnaires for completeness and for unclear responses immediately after completion. We will use Epidata version 3 software [40] to enter all data from the paper questionnaires and convert them into an electronic dataset. To reduce errors during data entry we will double-enter all the data. All data entrants will be trained on the meaning of variables and how they should be entered into the database. Questions that remain unanswered will be scored as ‘wrong’. The lead investigator will double-check the entries.

All copies of Consent Forms will be kept separate from the completed questionnaires and baseline characteristics of the participants. Both signed Informed Consent Forms and completed questionnaires will be kept under lock and key. All electronic data will be password-protected and kept on a separate hard disc, which will be backed up every week to prevent data loss. The hard discs will also be kept under lock and key and access will be restricted to study investigators.

Trial progress reports will be compiled by the study team and submitted to the regulatory bodies (Uganda National Council for Science and Technology and School of Medicine Research and Ethics Committee (SOMREC), Makerere University College of Health Sciences), in accordance with their respective guidelines. Final project reports (including trial reports) will be compiled by the study staff and submitted to the relevant bodies (Research Ethics Committees (RECs) and funders), as per their requirements.

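### The unblinded assistants who deliver the interventions also give, check and, for some participants, record the test behind both primary outcomes

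*Protocol article*

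**What the plan says.** The Blinding section states that "the research assistants who will deliver the intervention, the principle investigator supervising them, and the participants in the study will not be blinded". The reason given is the nature of the intervention. Only the statistician is kept unaware of which group is which.

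Delivery of the interventions gives the same pool of at least 20 assistants recruitment, "administration of the intervention, follow-up of participants in the community, and administration of the outcome assessment tool". It adds: "Each research assistant will be allocated about 25 participants to follow up through the duration of the study". Visits are weekly and include recaps of earlier episodes.

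Table 7, titled "Sample study procedures checklist for all participants", is headed by one research assistant. Its columns run from the participant's group, through every delivery visit, to the Claim Evaluation Tool.

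Outcome assessment says: "Research assistants will deliver the questionnaires, ensuring that the parents have adequate time to answer the questions". The assistants must also see that the questionnaires are fully completed. Data collection and management adds that "the research assistants will check the questionnaires for completeness and for unclear responses immediately after completion". An interviewer-administered, standardised Luganda audio version is provided "For participants who prefer listening to the Luganda version of the podcast but are unable to read Luganda", and for these people "A research assistant will enter their responses to the audio evaluation tool on a paper questionnaire". Items left unanswered are scored as wrong.

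**The concern.** The assistant knows the arm and, after weeks of playing the episodes, is likely to know what the podcast teaches. That same assistant is present at the test, may ask the participant to return to blank or unclear items, and for audio participants writes down the answers. If any of this is done differently in the two arms, the difference enters the number of correct answers. That number is one primary outcome, and cutting it at 11 of 18 gives the other. Neither primary outcome can act as a check on the other, because both use the same answers.

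An unblinded deliverer is unavoidable here. A tester who is also the deliverer is a choice, and the article gives no reason for it.

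**Working it through.** **Who does what.** The plan states no figure on this point, so the first step is to set the sections side by side.

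| Task | Who | Section |
|---|---|---|
| Deliver the interventions | Research assistants, unblinded | Delivery of the interventions; Blinding |
| Give the test and see it completed | Research assistants | Delivery of the interventions; Outcome assessment |
| Check for blanks and unclear answers | Research assistants | Data collection and management |
| Write down audio answers | A research assistant | Data collection and management |
| Analyse | Masked statistician | Blinding |

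No separate or masked tester is described. That the tester is the participant's own assistant is an inference from the caseload of about 25 held throughout and from the layout of Table 7.

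**What each safeguard reaches.**
- Closed multiple-choice items and a standardised recording narrow the room for judgement. They do not prevent prompting, re-asking or recording errors.
- Joint training and standard operating procedures aim at uniform conduct. They do not mask anyone.
- Double entry and the lead investigator's check protect the step from paper to database, after the answers are fixed.
- The masked statistician receives scores that were already settled in the field.
- Scoring unanswered items as wrong is a fixed rule. It also means that prompting someone to fill a blank can raise the score or leave it unchanged, never lower it.

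**Illustration of sensitivity.** Inputs from the document: 18 items, pass mark 11, 10% of controls passing, and 397 analysed with equal allocation, so 198.5 per arm. The figure of 397 is used only as the number analysed. Assumed: ability normal on the logit scale with SD 0.5 or 0.7, binomial answers given ability, the mean set so that 10% score 11 or more, no true effect, and no control helped.

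If a fraction f of podcast participants gains one correct answer, only those who would have scored exactly 10 cross the line:

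pass rate = 10% + f × P(score = 10)

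| | SD 0.5 | SD 0.7 |
|---|---|---|
| Mean score (SD of score) | 6.7 (2.8) | 6.1 (3.2) |
| P(score = 10) | 6.9% | 5.4% |
| f = 25% | 10 + 0.25 × 6.9 = 11.7% | 10 + 0.25 × 5.4 = 11.4% |
| f = 50% | 10 + 0.50 × 6.9 = 13.4% | 10 + 0.50 × 5.4 = 12.7% |
| f = 100% | 10 + 6.9 = 16.9% | 10 + 5.4 = 15.4% |

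**Effect on false-positive risk.** Take a podcast pass rate of 13%. The standard error of the difference is √[(0.10 × 0.90 + 0.13 × 0.87)/198.5] = 0.032, so the shift is 0.03/0.032 = 0.94 standard errors. The chance of a two-sided p below 0.05 is then about 16% instead of 5%.

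For the mean score, f = 50% is a shift of 0.5 items. The standard error is SD × √(2/198.5), which is 0.28 for SD 2.8 and 0.32 for SD 3.2. The chance of a significant result is about 34% to 42%.

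**The case against.** The article discloses the lack of blinding openly, and no figure is wrong. The rest of the case against is that the risk is small, partly inferred and not easily removed.

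- **Extent.** Most routes for judgement are closed by the multiple-choice format, and people outside the audio subset fill in a paper questionnaire themselves. A reader might infer that the audio route will be common, because pilot participants preferred Luganda. The document does not support that: the pilot difficulty was with reading English, whereas the audio version is for people unable to read Luganda. The share is not given and could be small or large.
- **Same assistant.** The data section says only that a research assistant records the answers, and Table 7 is a sample form. Who tests whom could be settled in the standard operating procedures, which are not shown. This stands as a caution, but the caseload rule makes the participant's own assistant the natural reading.
- **Direction.** A reader might infer that the bias must favour the podcast, or that assistants will read unclear answers generously. The article says neither. Assistants play recordings rather than teach, and the check is meant to reduce wrong entries and missing values. An assistant with participants in both arms would know the taught content when testing either. Bias needs different treatment of the arms; a tilt toward the podcast is plausible but not derivable.
- **Size.** The score model, its SD and the amount of help are all assumed. The 15-17% figure needs every podcast participant and no control to gain an answer. It shows how sensitive the pass mark is, not how large the bias is likely to be.
- **Remedy.** Participants keep the podcast on MP3 players, so the arm may come out at the visit, and follow-up is already expected to be difficult.

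These points limit the claim. None supplies a reason for the deliverer to give, check and record the test.

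**Conclusion.** The point holds in limited form. The article affirmatively assigns delivery and testing to the same unblinded staff, so this is a stated design choice and not a detail lost in condensing. Both primary outcomes are exposed, through prompting and on-the-spot checking for all participants and through recording for a subset of unstated size. The existing safeguards reduce the risk without masking the person who gives the test.

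The size of any bias cannot be derived from the document. Under the assumed model, modest help (one answer for a quarter to a half of the podcast arm) moves the pass rate by about 1 to 3 points against a target difference of 10. The mean score is the more sensitive outcome. This is worth correcting because correction is cheap; it is not evidence that the result will be biased.

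**What to change.** At the evaluation visit, and again at the 1-year assessment:

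1. Reassign the existing assistants so that none tests, records or checks answers for participants to whom they delivered.
2. Give the tester a list without study arm, which means leaving out the arm field of Table 6 and the group column of Table 7.
3. Where feasible, have audio participants indicate their own answer to the recorded item. The response format needs a short trial with people who cannot read Luganda.
4. Apply one fixed rule, blind to arm, to unclear or double-marked answers.

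No additional staff or visits are needed. The costs are added scheduling and travel, a less familiar visitor with some possible effect on retention, and the loss of some answers that field clarification would have rescued. Masking will be only partial, because participants keep the MP3 player and may reveal their arm, and testers from the same pool still know the taught content. If reassignment proves impracticable, state the limitation and report the primary outcomes by mode of administration.
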